### Control condition: standard care

Patients who are assigned to the control condition will receive the standard rehabilitation program, in order to be able to study the additional effect of the intervention to the standard rehabilitation program. This standard rehabilitation program consists of individualized amounts of treatment by a physical therapist, occupational therapist, speech therapist, psychologist, social worker, and rehabilitation physician, depending on the severity of stroke. On average, stroke patients in outpatient rehabilitation receive twelve hours of treatment a week during a nine week rehabilitation program.

### Outcomes

Primary outcome measures are changes in task-oriented coping and psychosocial HR-QoL in patients in the intervention group in comparison with the control group. Coping style is measured using the Coping Inventory for Stressful Situations (CISS) and the short version of the Social Problem Solving Inventory-Revised (SPSI-R:SF). The CISS questionnaire consists of 48 questions and contains three subscales; Task-oriented coping, Emotion-oriented coping, and Avoidant coping. The subscale Avoidant coping consists of two subscales; Distraction and Social Diversion
[18,19]. Because the PST aims at tasks, ‘Task-oriented coping’ is chosen as a primary endpoint; the other two subscales are used as secondary endpoints. The SPSI-R:SF questionnaire consists of ten questions about problem solving skills regarding daily situations. There are five subscales: Positive Problem Orientation, Rational Problem Solving, Negative Problem Orientation, Impulsivity/Carelessness Style, and Avoidance Style, and all are used as secondary endpoints in this trial
[20].

HR-QoL is measured using the EuroQol (EQ-5D-5L) and the Stroke Specific Quality of Life Scale (SS-QoL-12). The EQ-5D is a generic questionnaire, and consists of five questions regarding mobility, self-care, daily activities, pain/complaints, mood, and a VAS scale. The five dimensions can be combined to one utility scale, representing the societal perspective of the general public
[21]. The SS-QoL-12 is specifically developed for the population of stroke patients
[22]. We will use the abbreviated version containing twelve items, which has been shown valid
[23]. The questionnaire provides a total score and two sub scores: physical and psychosocial, of which the psychosocial sub-score is defined as the primary endpoint. The other HR-QoL scores are used as secondary endpoints.

Other secondary outcome measures are differences in depression, social participation, and health care consumption between patients in the intervention and control group. Additionally, the influence of cognitive functioning, personality characteristics, aphasia, type of stroke, side of stroke, level of functioning, and demographic characteristics on the outcomes will be assessed. Finally, the cost-effectiveness of the intervention will be calculated compared with standard care.

Depression is measured using the Center for Epidemiologic Studies Depression Scale (CES-D). This questionnaire consists of twenty items concerning depression, higher scores indicate more depressive symptoms
[24].

Social participation is measured using the Impact on Participation and Autonomy (IPA). The questionnaire consists of five dimensions; Autonomy indoors, Family role, Autonomy outdoors, Social life and relationships, Work and education
[25].

Health care consumption is measured using the Trimbos Questionnaire for Costs association with Psychiatric Illness (TiC-P). The questionnaire was developed for economic evaluation in mental health care, and measures health care consumption and productivity losses
[26].

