### Objectives

The primary aim of this study is to investigate whether PST is an effective group intervention for improving active problem-focused coping style and HR-QoL in stroke patients. The secondary aim is to determine the effect of PST on depression, social participation, health care consumption, and the cost-effectiveness of the intervention. The effectiveness of the therapy will be investigated in an open group design, which has not been used in PST research before. PST will be added to the standard care just before the end of the rehabilitation program, as at this moment a relapse in HR-QoL is frequently observed, when patients cannot rely on their therapists anymore
[16]. By teaching patients to actively cope with stressful situations, through adapting and realizing their goals, we expect that patients will use more effective coping styles, which consequently may prevent the relapse in HR-QoL, and possibly increase HR-QoL in the long term. With regard to the secondary aims of this study, we expect the incidence of depression to decrease, social participation to improve, and health care consumption to decrease, resulting in a favorable cost-effectiveness ratio for the intervention.

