### Sample size calculation

To determine the sample size for measuring differences between the intervention- and control group in coping style and HR-QoL, we searched for comparable effect sizes in the literature. With regard to coping style, there was no data available for this calculation. With regard to HR-QoL, Studenski (2005) measured an increase in HR-QoL after a physical therapy for stroke patients, with a long term effect size f ranging from 0.06 to 0.18
[27]. Because of the lack of more comparable data, we used this data and carefully estimated the effect size f to be 0.08. Considering the design of two groups and four repeated measurements, an expected correlation of 0.70, an alpha of 0.05, and a power of 0.80, we calculated a total required sample size of 132 patients based on the F-test. Because potential drop out is estimated at 0.30, we will strive to include 200 patients.

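### Two primary endpoints, but alpha and power are set for one test, so either the 5% error rate or the 80% power fails for a single claim of effectiveness, depending on an unstated rule

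*Protocol article*

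**What the plan says.** The Outcomes section of the protocol article sets two primary endpoints: "Primary outcome measures are changes in task-oriented coping and psychosocial HR-QoL in patients in the intervention group in comparison with the control group". It picks the CISS task-oriented subscale for coping. For the SS-QoL-12 it names the psychosocial part, "of which the psychosocial sub-score is defined as the primary endpoint".

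The Objectives section asks whether PST is an "effective group intervention for improving active problem-focused coping style and HR-QoL in stroke patients". It joins the two outcomes with a plain conjunction and does not say whether a positive result needs both or only one.

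The Sample size calculation section says it concerns differences in both coping style and HR-QoL. It reports that no data were available for coping, takes f = 0.08 from HR-QoL data, and makes one calculation, using an F-test: "an expected correlation of 0.70, an alpha of 0.05, and a power of 0.80, we calculated a total required sample size of 132 patients". With dropout put at 0.30, the target becomes 200.

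The Statistical analyses section fits a separate linear mixed model to every primary and secondary outcome, with time, group and their interaction. It gives no alpha split, no order of testing and no joint criterion for the two primaries.

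**The concern.** An alpha and a power belong to a decision rule. With one primary test the rule is obvious. With two it is not, and the choice changes what the stated 5% and 80% mean.

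The practical risk is a split result. The Objectives section expects coping to change first and HR-QoL to follow from it, so a significant coping result beside a non-significant HR-QoL result is plausible. The text then cannot say whether PST has been shown to be effective, and the question could be settled after the results are known. The Discussion speaks of the intervention proving effective as a single conclusion, so a rule is needed.

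**Working it through.** **Inputs from the protocol article.** Two groups, 1:1; m = 4 measurements; correlation ρ = 0.70; f = 0.08; alpha 0.05; power 0.80; stated N = 132; dropout 0.30; target 200.

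**Assumptions not in the article.** The correlation between the two primary outcomes (shown from 0 to 0.9), and f = 0.08 for coping as well as HR-QoL.

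**1. Reproduce the stated figure.** For the group-by-time interaction F-test with sphericity, λ = f²·N·m/(1 − ρ), df1 = (2 − 1)(4 − 1) = 3 and df2 = (N − 2)·3.
- At N = 132: λ = 0.0064 × 132 × 4 / 0.30 = 11.26, df2 = 390, power = 0.810.
- At N = 130: power = 0.803. This is the smallest N reaching 0.80, within 2 patients of the stated 132.
- A between-groups F-test would need 954 patients and does not fit.
- Dropout: 132/0.70 = 188.6, so 189. The target of 200 covers this and leaves 200 × 0.70 = 140 completers, at which power is 0.835.

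The calculation is sound for one test of one outcome. It contains no allowance for a second primary.

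**2. Either endpoint suffices, each at 0.05.** For independent outcomes the family-wise error is 1 − 0.95² = 0.0975. For correlated outcomes, two 3-df tests were simulated:

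| Correlation | Family-wise error | Power for at least one, N = 132 |
|---|---|---|
| 0 | 9.8% | 0.97 |
| 0.3 | 9.6% | 0.94 |
| 0.5 | 9.2% | 0.92 |
| 0.7 | 8.5% | 0.90 |
| 0.9 | 7.2% | 0.86 |

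The 5% fails; the 80% is exceeded.

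**3. Both endpoints required, each at 0.05.** The error rate cannot exceed 5%. Joint power under independence is 0.810² = 0.66 at 132 and 0.835² = 0.70 at 140 completers. By simulation at N = 132 it is 0.70 at correlation 0.5, 0.73 at 0.7 and 0.76 at 0.9. The 5% holds; the 80% fails.

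**4. Holm across the two.** Single-endpoint power at alpha 0.025 is 0.725 at 132 and 0.756 at 140. Under Holm an endpoint is rejected if its p is at most 0.025, or if its p lies between 0.025 and 0.05 and the other p is at most 0.025. With both effects present and independence, per-endpoint power is:
- N = 132: 0.725 + (0.810 − 0.725) × 0.725 = 0.79
- N = 140: 0.756 + (0.835 − 0.756) × 0.756 = 0.82

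If only one outcome has an effect, the second term is multiplied by 0.025 instead, and power is close to the 0.025-level values of 0.72 and 0.76.

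**5. Fixed order, coping then HR-QoL, each at 0.05.** Power for coping is 0.81 at 132 and 0.83 at 140. Power for HR-QoL is the joint power from step 3: 0.66 and 0.70 under independence.

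**The case against.** The strongest reply is that a multiplicity rule is ordinary SAP content. Neither the SAP nor the full protocol is shown, and the sample size arithmetic is correct. This stands as far as the missing rule alone goes. It does not cover the sample size section, which says it serves both outcomes while fixing an alpha and a power that belong to one test. A later rule would have to live with those figures or restate them.

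A second reply is that the trial asks two separate questions, each answered by its own model at 0.05. On that reading the per-endpoint figures stand as stated, subject to f = 0.08 for coping. That is fair, but it gives no error rate for the single conclusion that PST is effective, which is how the Objectives and Discussion sections put it.

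Two stronger readings are tempting and are not supported. A reader might infer that neither the 5% nor the 80% holds under any rule; steps 2 and 3 show that each rule breaks one and keeps the other. A reader might also count separate tests at T1, T2 and T3 for each outcome and arrive at a much larger error rate. The article plans no such visit-by-visit testing at 0.05: it specifies a model with an interaction term, and the sample size matches one 3-df F-test per outcome.

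**Conclusion.** The point holds in limited form and should be fixed; it does not undermine the design. For a single claim of effectiveness, the stated pair of 5% error and 80% power cannot both be met with two primaries tested separately at 0.05. Depending on the rule, the trial has a family-wise error of about 7% to 10%, or joint power of about 0.66 to 0.76 at 132 patients (about 0.70 at 140 completers under independence).

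The error figures depend on the assumed correlation between the outcomes. The power figures also assume f = 0.08 for coping, which the article says it had no data to support. Independence is the least favourable case shown, and the article's own reasoning that coping drives HR-QoL makes some positive correlation likely.

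**What to change.** Before any unblinded analysis, state one decision rule for the two primary endpoints and restate the power that goes with it.

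Preferred: Holm, with the smaller p-value tested at 0.025 and, if significant, the other at 0.05. This holds the family-wise error at 5% and lets either endpoint succeed alone. Report power as about 0.79 per endpoint at 132 and 0.82 at 140 completers if both effects exist and the outcomes are independent, and about 0.72 and 0.76 if only one does.

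Alternative: a fixed order, with task-oriented coping at 0.05 and then psychosocial HR-QoL at 0.05 only if coping is significant. This follows the causal chain in the Objectives section. Its drawback is that HR-QoL is then gated behind the endpoint with no effect-size data.

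The sample size section should also say that f = 0.08 is an assumption for coping. The cost is a few sentences and a more qualified power statement. N stays at 200. For comparison, a plain 0.025 split with 80% power per endpoint would need 154 evaluable patients, or 154/0.70 = 220 randomised.

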### Sample size calculation

To determine the sample size for measuring differences between the intervention- and control group in coping style and HR-QoL, we searched for comparable effect sizes in the literature. With regard to coping style, there was no data available for this calculation. With regard to HR-QoL, Studenski (2005) measured an increase in HR-QoL after a physical therapy for stroke patients, with a long term effect size f ranging from 0.06 to 0.18
[27]. Because of the lack of more comparable data, we used this data and carefully estimated the effect size f to be 0.08. Considering the design of two groups and four repeated measurements, an expected correlation of 0.70, an alpha of 0.05, and a power of 0.80, we calculated a total required sample size of 132 patients based on the F-test. Because potential drop out is estimated at 0.30, we will strive to include 200 patients.

### Statistical analyses

Demographic variables will be analyzed with an independent sample T-test for continuous variables, the Mann–Whitney U test for ordinal variables, and the chi-square test for categorical variables. Linear Mixed Models will be used to compare the repeated measurements between treatment groups, taking into account the correlation within and between subjects. We will create models for all the primary and secondary outcome variables, with time, group condition (intervention or control), and the interaction between these variables as predictors. Furthermore, we will control for variables that are accidentally not equally distributed between the two group conditions.

The cost-effectiveness of the intervention will be calculated by counting all the medical and non-medical costs, like productivity losses. The incremental cost-effectiveness ratio will be calculated by dividing the difference in total costs by the difference in quality-adjusted life years (QALYs). These QALYs will be calculated based on the EQ-5D questionnaire. The economic evaluation will be conducted according to the Dutch guidelines
[28] and includes multivariate probabilistic sensitivity analyses. In the base case scenario the time horizon will be one year. If the effect is still present at one year follow up, a Markov model will be made to model a longer time horizon.

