## Methods/design

### Study design and procedure

The effectiveness of PST for stroke patients will be evaluated in a multicenter pragmatic randomized controlled trial (RCT) with one year follow-up, with the intervention performed in the daily practice of a sub-acute outpatient stroke rehabilitation program. As such, the potential effects of the intervention have a good external validity, which allows us to calculate the cost-effectiveness of the therapy compared with standard care.

The study will be performed in Rijndam Rehabilitation Center in collaboration with Erasmus MC, both in the Netherlands, and in Ghent University Hospital in Belgium. Patients are invited by their rehabilitation physician to participate in the study. Before the start of the study, patients need to sign the informed consent form. Data will be collected at four time points by one of three research psychologists. T0 is the baseline measurement, performed within three weeks before the start of the intervention phase. T1 will be performed within ten days after the intervention phase, T2 six months and T3 twelve months after the intervention phase (Figure 
1). The measurements will be performed in the rehabilitation center or at the patients’ home in a face-to-face interview. The study has been approved by the Medical Ethics Committee of Erasmus MC University Medical Center and the Ethics Committee of Ghent University Hospital.

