### Randomization

Patients are randomized to the intervention- or control condition using a stratified block randomization procedure with a block size of four. To ensure comparability between the two groups, patients are stratified per rehabilitation center. A member of the research group, who is not involved in the collection of the data, prospectively allocates the patients to the intervention- or control condition in a one-to-one ratio using an online random-number generator. To allow blinded randomization, the allocation information will be put in separate sealed envelopes which are consecutively numbered. At the end of the baseline measurement, the investigator opens the numbered envelop and informs the patient about the condition he or she is assigned to. The research psychologists who perform the baseline and follow-up measurements are blinded for treatment condition. The therapists who provide the intervention are not involved in the collection of the data. The investigator who will analyze the data is not involved in the collection of the follow-up measurements.

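### Covariates are to be chosen by chance imbalance with no criterion, and the stated model leaves T0 free and omits centre: a free gain in precision and pre-specification is missed, though the analysis is valid

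*Protocol article*

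**What the plan says.** Under Statistical analyses, the protocol article plans linear mixed models for every primary and secondary outcome, "with time, group condition (intervention or control), and the interaction between these variables as predictors". It then adds: "Furthermore, we will control for variables that are accidentally not equally distributed between the two group conditions". No covariate is named, and no criterion for imbalance is given. The only comparison of the arms at baseline that the section describes is significance testing, which begins: "Demographic variables will be analyzed with an independent sample T-test for continuous variables", with rank and chi-square tests for the other variable types.

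Under Randomization, allocation is made "using a stratified block randomization procedure with a block size of four" and "in a one-to-one ratio using an online random-number generator". The stratum is the centre: "To ensure comparability between the two groups, patients are stratified per rehabilitation center". Under Study design and procedure, "T0 is the baseline measurement, performed within three weeks before the start of the intervention phase". The allocation envelope is opened only at the end of that visit. The sample size calculation counts four repeated measurements, so T0 is treated as one of the responses.

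**The concern.** In a trial randomised as described, any baseline difference between arms is due to chance, so testing for one answers no useful question. A covariate improves an analysis when it predicts the outcome; imbalance is a poor guide to that. Without a list or a threshold, the final model is unknown until the arms have been compared, and several models could claim to follow the plan.

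Two things the design already supplies are also left out of the stated model. T0 is measured before allocation is disclosed, so the true T0 means are equal in the two arms; a model with a free group difference at T0 spends information estimating a quantity known to be zero. Centre restricted the randomisation but is not among the predictors. At stake are precision and a primary model that can be shown to have been fixed beforehand.

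**Working it through.** **Inputs.** From Sample size calculation: f = 0.08, 2 groups, 4 measurements, correlation 0.70, alpha 0.05, power 0.80, N = 132, dropout 0.30, target 200. Assumed: compound symmetry, equal arms and complete data, except where stated.

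**1. The plan's own figure.** For the time-by-group F-test, λ = f² × N × m / (1 − ρ), with df 3 and 3(N − 2).
- At N = 132: λ = 0.0064 × 132 × 4 / 0.30 = 11.264, df 3 and 390, power 0.81.
- The smallest N reaching 80% is 130 (power 0.803), so 132 reproduces within two patients.
- A pure between-group F-test at the same f would need 953. The calculation therefore rests on the interaction test, with T0 as a response.
- Dropout: 132 / 0.70 = 188.6, so 189; 200 × 0.70 = 140 completers, power 0.835.

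**2. Precision from using T0.** Variances are per patient, in units of the outcome variance; the difference between two equal arms has 4/N times this.
- One visit, T0 free: 2(1 − 0.70) = 0.60. T0 means constrained equal, or T0 as covariate: 1 − 0.70² = 0.51. Ratio 0.85; the standard error falls by 7.8%.
- Mean of T1 to T3: the variance of the mean is (1 + 2 × 0.70)/3 = 0.80. Free: 0.80 + 1 − 1.40 = 0.40. Constrained: 0.80 − 0.49 = 0.31. Ratio 0.775.
- At one visit the ratio is (1 + ρ)/2: 0.75, 0.80, 0.85 and 0.90 for ρ = 0.5, 0.6, 0.7 and 0.8.

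**3. Power of the 3-df test at N = 132.** Each effect pattern is scaled so that the free-T0 model has λ = 11.264 and power 0.81. For the constant pattern, for example, the constrained λ is 11.264 × 0.40/0.31 = 14.53.

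| Pattern | Effect at T1, T2, T3 (SD) | λ, constrained | Power, constrained | N for 80% (130 if free) |
|---|---|---|---|---|
| Constant | 0.37, 0.37, 0.37 | 14.53 | 0.905 | 101 |
| Linear growth | 0.143, 0.286, 0.429 | 13.23 | 0.873 | 111 |
| T3 only | 0, 0, 0.37 | 11.63 | 0.823 | 126 |

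A linearly fading effect gives the same result as linear growth.

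**4. What the imbalance rule does to the tested term.** Group-by-time coefficients compare within-patient changes between arms. A time-constant covariate entered as a main effect adds the same amount at every visit and cancels. In simulated complete data (140 patients, 4 visits) the estimates agreed to five decimals with and without it. With dropout (assumed: N = 200, 30% outcome-dependent dropout, ρ = 0.70, 10 covariates with joint R² 0.30, selection at 5%), when a covariate was selected the T3 estimate moved by at most 0.07 standard errors in 95% of runs.

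**5. Type I error.** An illustrative regression of a single outcome (assumed: N = 132, five covariates, joint R² 0.30) gave 0.043 for adjusting whenever a 5% test is significant, and 0.053 for a fixed covariate set. Taking the smallest p-value over no adjustment and thresholds of 5%, 10% and 20% gave 0.063.

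**6. How often the rule would fire.** The number of variables is not in the document. With k independent variables tested at 5%, 1 − 0.95^k is 14% for 3, 30% for 7, 40% for 10 and 54% for 15.

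**7. Centre.** Blocks of four at 1:1 limit imbalance to two patients per centre, so an imbalance rule would almost never select it. No between-centre variance is given, so the gain from including it cannot be computed.

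**The case against.** The case for leaving the plan alone is strong in several respects. A mixed model with time, group and interaction is standard, valid under randomisation and consistent with the sample size calculation. Read literally, the covariate rule adds main effects only, and step 4 shows these hardly touch the tested term. The same argument applies to centre as a main effect. The article does not say that the baseline tests trigger adjustment; that link is inferred, and the tests are described for demographic variables only. A condensed article may also leave the full covariate list and the handling of T0 to an analysis plan that is not shown.

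Most of this stands. A reader might infer that the rule biases the primary result or inflates its type I error. The document does not support that: applied mechanically, the rule is slightly conservative, and the inflation in step 5 needs someone to choose among thresholds after seeing results, which the plan does not propose. A reader might also take 0.40/0.31 = 1.29 to mean that the trial forgoes the equivalent of 29% more patients. That is the favourable case. It needs an effect constant over T1 to T3; for an effect at T3 alone the saving is 130 to 126. The article's Objectives speak of preventing a relapse and possibly of a long-term increase, so a late effect is plausible.

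What the objection does not remove is that the imbalance rule and the list of predictors are stated choices. The rule selects on the wrong property and without a criterion, and the stated model does not use what randomisation and stratification provide. An unseen plan might add centre or T0 adjustment, so that part is less certain than the rule itself.

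**Conclusion.** The point holds as a costless improvement in precision and pre-specification. It is not a bias, an error in the sample size or a threat to the validity of the primary comparison.

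The gain comes chiefly from T0: 15% less variance at one visit at the plan's own correlation. At N = 132, power goes from 0.81 to between about 0.82 and 0.90, depending on when the effect appears. These figures rest on compound symmetry, complete data and ρ = 0.70; a higher correlation gives a smaller gain at one visit. No figure can be put on centre. The 14% to 54% chance of at least one nominal imbalance rests on an assumed 3 to 15 independent variables. It shows how readily chance could alter the covariate set, not how much harm would follow.

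**What to change.** - Remove the imbalance-triggered adjustment from the primary models, or keep it only as a labelled sensitivity analysis.
- Show baseline characteristics by arm descriptively, without significance tests.
- Fix the model in advance for each outcome: time, and group by post-baseline visit with T0 means constrained equal across arms (or the T0 value as a covariate, by time), plus centre by time.
- If more covariates are wanted, name a few prognostic ones before the arms are compared and enter them by time. Age and level of functioning are candidates, because the article already plans to examine level of functioning and demographic characteristics.

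The cost is a change of analysis wording. It needs no new data and no more patients, and the planned sample of 200 can stay.
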